### Participant timeline {13}

After providing informed consent, participants complete screening assessments within 28 days prior to baseline, including demographic and medical history (with past falls), eligibility confirmation, and in-person testing with the 6MWT, TUG, and TMT A and B.

Baseline assessments are conducted within 14 days before starting the intervention and include the PHQ-8, PROMIS Social Isolation Scale, BI, and falls/adverse event documentation. Participants then complete a 12-week intervention phase with three MR-001 walking sessions per week, supported by engagement calls. Primary and secondary outcomes are reassessed at the end of week 12. Follow-up visits at weeks 16 and 24 evaluate maintenance of effects during the washout period.

Randomization occurs at the end of week 24, assigning participants to either cohort A, which receives the MR-001 intervention for another 12 weeks (weeks 25–36), or cohort B, which continues washout. Outcome assessments are repeated at weeks 36 and 48. Claims re-authorization is performed, as needed, and healthcare utilization data are collected throughout the study with a final follow-up call conducted at approximately week 60 to ensure collection of 52 weeks of HCRU data. The participant timeline detailing the schedule of enrollment, interventions, and assessments is illustrated in Table 1.

**Table 1 Tab1:** Participant timeline

	Step 1						Step 2			
	Screening	Baseline (T1)	Intervention Step 1	Post- Intervention (T2)	Follow Up 1 (T3)	Follow-Up 2 (T4)	Intervention Step 2/Cont. Washout	Follow-Up 3 (T5)	Follow-Up 4 (T6)	Follow-Up call (as needed)
**Timepoint**	Day −28 to day 0	Day −14 to Day 0	Weeks 1–12	End of week 12 (+/- 7 days)	End of week 16 (+/- 7 days)	End of week 24 (+/- 7 days)	Weeks 25 - 36	End of week 36 (+ 14 days)	End of week 48 (+ 28 days)	Through Week 60
**ENROLLMENT**										
Informed consent	X									
Demographics & Med hx	X									
Eligibility screen	X									
Claims data consent	X									X
Randomisation						X				
**INTERVENTIONS**										
MR-001 (3x/week)			X				X (Cohort A only)			
**ASSESSMENTS**										
6-Minute Walk Test	X			X	X	X		X	X	
Timed Up and Go	X			X	X	X		X	X	
Trail Making Test A & B	X			X						
Patient Health Questionnaire-8		X		X	X	X			X	
PROMIS Social Isolation		X		X	X	X			X	
Barthel Index		X		X	X	X				
Falls/AE collection		X	X	X	X	X	X	X	X	X

### Sample size {14}

The target enrollment is 225 participants, allowing for an anticipated 20% attrition to yield approximately 180 participants completing the study. The calculation is based on the primary endpoint of device engagement, tested using a one-sided binomial proportion test with alpha = 0.05 against a null hypothesis of 60% engagement. Assuming a true engagement rate of 72%, this sample size provides 98% power to reject the null. Exploratory analyses will also assess engagement thresholds of 70% and 80%.

### Recruitment {15}

Participants are identified through a multi-step, IRB-approved strategy combining digital outreach, clinical referrals, and community engagement. The primary method of recruitment is via targeted digital advertising within ~50 miles of assessment center, distributed through multiple recruitment vendors, including 1nHealth, Goodlab, 1Digital, and Clinical Connection. Referrals also come from stroke specialists, rehabilitation providers, patient advocacy groups, support networks, and, where permitted, healthcare system databases. While recruitment methods are focused on a 50-mile radius from a physical assessment center, participants are not excluded from the study in the pre-screener if they live at a greater distance as described further below.

All referred individuals are directed to a centralized study landing page that contains general study information, frequently asked questions (FAQs), a pre-screener link, and gait demonstration videos. Interested individuals complete an online pre-screener, allowing them to self-attest to key inclusion and exclusion (I/E) criteria. Individuals who screen out due to being less than 6 months post-stroke are flagged for re-contact at a later date. During the pre-screener, participants are provided with a list of all physical assessment locations and asked if they are willing to travel to one. If they decline, they are disqualified; if they agree, regardless of proximity, they may proceed to the eligibility call.

Participants meeting pre-screener criteria are invited to an eligibility call with the study team. Real-time call initiation is supported, along with the ability to schedule calls with study staff within the following few weeks. Participants receive automated reminders before scheduled calls, and coordinators proactively reach out to candidates to support scheduling. During the eligibility call, trained team members confirm I/E criteria and initiate the informed consent process.

Eligible participants then attend an in-person screening visit at a physical assessment location. Data and source documentation collected during in-person screening are uploaded into CRIO, including walking videos to determine walking safety. Study investigators review all submitted materials to make the final eligibility determination. Those deemed eligible move forward to baseline visit planning, which includes scheduling of the baseline assessment and a guided setup call. The study kit is shipped from the distribution center (C3i Solutions, Pittston, PA) to arrive ~3–5 days before the guided setup call.

This stepwise, digitally coordinated recruitment strategy, with evolving process improvements and human support, is designed to minimize friction, support participant comfort, and promote successful enrollment in a decentralized study design.

#### Mid-study adaptations

After study initiation, trial monitoring revealed an opportunity for several operational refinements to ensure successful completion of the trial objectives. These included assigning a dedicated participant coordinator to reduce missed eligibility calls, allowing informed consent and claims authorization to be completed in separate calls based on participant preference, expanding the number of assessment centers from 30 to 33 to increase geographic reach and increase recruitment capacity, and refining outreach workflows to enhance scheduling efficiency. All adaptations were made in response to observed challenges with trial operation and based on participant feedback. These changes did not alter the study objectives, endpoints, or analytic plan.

## Assignment of interventions: allocation

### Sequence generation {16a}

Randomization for Step 2 is performed using Python’s built-in random shuffle function. Participants are randomized in a 1:1 ratio to either receive another 12 weeks of MR-001 intervention (cohort A) or continue washout for an additional 24 weeks (cohort B).

### Concealment mechanism {16b}

The randomization sequence is generated by the CRO and implemented through Ripple Science (Ann Arbor, MI), the Clinical Trial Management System (CTMS) for this trial. Site personnel do not have access to the randomization sequence prior to participant allocation. Randomization assignments may be revealed only after all Step 1 assessments are completed and data are entered into the system.

### Implementation {16c}

Eligible participants who complete Step 1 are randomized at the week 24 visit. The CTMS automatically assigns participants to their allocated cohort after completion of all required week 24 assessments. Site personnel communicate the assignment to participants and initiate the appropriate Step 2 procedures.

## Assignment of interventions: blinding

### Who will be blinded {17a}

This is an open-label study during Step 2. Participants and investigators are unblinded to cohort assignment following randomization. However, outcome assessors conducting in-person gait assessments are blinded to cohort assignment. Data analysts remain blinded to treatment assignment until database lock.

### Procedure for unblinding if needed {17b}

As this is an open-label study during the randomized phase, formal unblinding procedures are not applicable. However, in cases where knowledge of previous intervention exposure is critical for safety decisions, complete treatment history is available to investigators for review.

## Data collection and management

### Plans for assessment and collection of outcomes {18a}

Data collection occurs through multiple mechanisms:

In-person assessments: Conducted at clinical research assessment centers for gait performance assessments (6MWT, TUG) and cognitive assessments (TMT A and B). Trained personnel conduct assessments according to standardized protocols.Remote assessments: Patient-reported outcomes (PHQ-8, BI, PROMIS Social Isolation Scale) are collected electronically through secure platforms.Device data: The MR-001 system automatically captures session data, adherence metrics, and technical performance indicators.Healthcare utilization data: Claims data is obtained from insurance providers and healthcare systems with appropriate participant authorization and data use agreements through Flexpa.

### Plans to promote participant retention and complete follow-up {18b}

To promote participant retention and ensure complete follow-up, the study implements several engagement strategies. These include regular communication and personalized support from study staff, as well as flexible scheduling options to accommodate participants’ availability. In addition, weekly emails are sent while a participant has MR-001 to increase engagement touchpoints. Participants receive compensation for their time and travel expenses. Additionally, travel support to all in-person visits via study staff-scheduled Lyft or Uberhealth rides is provided for those who request the additional support.

### Data management {19}

Data is collected and managed using Clinical Research IO (CRIO), a 21 CFR Part 11-compliant electronic source and electronic data capture (eSource/EDC) system. During in-person assessments, staff performing the physical assessments capture the data using paper source, which is then entered into CRIO. The paper source documentation is also uploaded into CRIO for source data verification (SDV) to ensure the data entered matches the source documentation. Any discrepancies are queried with the site. Data collected during remote assessments is entered directly into CRIO without paper source. Built-in edit checks and role-based access controls ensure data accuracy, integrity, and security. All data entries are time-stamped and audit-trailed to facilitate regulatory compliance. Source document verification is performed according to the monitoring plan.

Data quality is ensured through:

Real-time data validation and query generationRegular data review meetingsSource data verificationDouble data entry for critical variablesAutomated range and consistency checks

The study design includes a phased database lock strategy, with multiple database locks planned following completion of key study timepoints. Specifically, database locks will occur after all participants have completed their 3-month, 6-month, and final study visits. This approach supports timely data dissemination while preserving data integrity.

Each database lock will occur only after all data queries have been resolved and all monitoring activities completed for the relevant study visit. As all data required for each pre-specified endpoint will have been collected prior to lock, no adjustments to the planned alpha level will be necessary for the corresponding analyses. Changes to the database after lock will not be permitted unless predefined unlock criteria are met and appropriately documented.

### Confidentiality {27}

All study data is handled in accordance with applicable privacy regulations, including HIPAA. Participants are assigned unique study identification numbers, and all data is de-identified for analysis purposes. Access to identifiable information is limited to authorized study personnel with documented training in data privacy and confidentiality.

Data sharing agreements are established with all parties handling participant data, including technology vendors and data analysis contractors. All electronic data will be encrypted and stored on secure servers with appropriate backup and disaster recovery procedures.

### Plans for collection, laboratory evaluation, and storage of biological specimens for genetic or molecular analysis in this trial/future use {33}

n/a—No biological specimens are collected in this study.

## Statistical methods

### Statistical methods for primary and secondary outcomes {20a}

Primary analysis: The primary endpoint is engagement with MR-001, defined as the proportion of participants achieving at least moderate engagement. Engagement will be categorized as low, moderate, or high based on predefined thresholds of weeks, sessions, and minutes of use. The primary hypothesis is that the proportion of participants achieving at least moderate engagement exceeds a benchmark of 60%. Sensitivity analyses will be conducted at thresholds of 70% and 80%. A one-sided binomial proportion test will be used at significance level *α* = 0.05. Participants who initiate the intervention but withdraw from the study prior to completion of the planned intervention will be classified as non-engaged in the primary analysis.

Secondary analyses: Secondary endpoint analyses will evaluate mean changes from baseline to post-intervention for walking endurance (6MWT), depressive symptoms (PHQ-8), independence in activities of daily living (BI), social isolation (PROMIS Social Isolation Scale), and cognitive and executive function (TMT A and B).

Durability of walking endurance will be assessed at 16-week and 24-week follow-up visits after discontinuation of the intervention at 12 weeks. Results at these follow-up visits will be compared with the post-intervention assessment to determine whether the gains achieved during treatment are sustained. The analysis will be conducted using a non-inferiority framework, with a pre-specified margin of one-half of the minimal clinically important difference (17.2 m) [52]. This approach is designed to test whether the benefits observed during the intervention period are retained after device use is discontinued. Linear mixed modeling (LMM) will be used to estimate the changes over time. Random intercepts and/or modeling the covariance matrix of the error terms will be used to account for repeated measures. Model choices will be made based on minimizing Akaike Information Criteria (AIC) and Bayesian Information Criteria (BIC). Age, sex, baseline speed, and time since stroke will be evaluated and included as covariates if they are predictive of the change scores.

### Interim analyses {21b}

A single interim analysis for futility will be conducted when approximately 50% of participants have completed Step 1. The analysis will focus on the primary engagement endpoint and safety data. The study may be terminated early if engagement rates are substantially lower than expected or if safety concerns arise. No formal stopping rules for efficacy are planned, as this would require adjustment of the overall alpha level.

### Methods for additional analyses (e.g., subgroup analyses) {20b}

#### Exploratory analyses

Exploratory analyses are planned to provide additional insight into the effects of MR-001 and to identify factors that may influence treatment response. These will include:

Change in general mobility (TUG): Mobility will be assessed at multiple study visits across the intervention, follow-up, and re-treatment phases. Analyses will explore whether the MR-001 intervention is associated with sustained or progressive improvements in functional mobility, as well as whether gains are maintained after withdrawal or re-established with re-treatment.Clinical responsiveness: Participants who achieve at least the minimal clinically important difference (MCID) on the 6MWT will be classified as responders. This analysis will help quantify the proportion of patients experiencing a clinically meaningful benefit, complementing the mean change analysis.Predictors of response: Baseline demographic and clinical characteristics, as well as engagement levels with the device, will be examined as potential predictors of responder versus non-responder status. This analysis is intended to inform which subgroups may benefit most from the intervention.Durability of re-treatment: Among participants who undergo a second round of intervention following the withdrawal phase, changes in walking mobility and endurance will be compared before and after re-treatment to assess whether the intervention effect can be re-established.

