### Objectives {7}

This study aims to evaluate user patterns of engagement, clinical effectiveness, durability of response, and health economic impact on participants post-stroke who complete the MR-001 intervention in the home setting. The primary objective is to assess engagement with the MR-001 neurorehabilitation system, measured by the proportion of participants achieving at least moderate engagement over the 12-week intervention period. The secondary objectives are to evaluate: (1) the effects of MR-001 on walking endurance, as measured by the 6-Minute Walk Test (6MWT); (2) the durability of this effect following 12 weeks of intervention; and (3) the effects of MR-001 on health-related quality of life, activities of daily living, social isolation, and cognition and executive function. Exploratory objectives include assessing: (1) changes in general mobility, as measured by the Timed Up and Go Test (TUG); (2) the effects of a second period of treatment on walking endurance and general mobility following a 3-month no-intervention period; (3) the differential intervention effects across subgroups (e.g., engagement and baseline gait impairment subgroups); (4) the proportion and predictors of responders; and (5) healthcare resource utilization, assessed through claims data analysis.

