### Trial design {8}

This longitudinal, pragmatic, decentralized hybrid trial integrates home-based implementation of the MR-001 therapy with selected controlled trial elements to maximize external validity while maintaining scientific rigor. In this study, “home-based” refers to any environment outside of a professional healthcare facility consistent with the FDA definition [39]. A two-step, withdrawal with randomized re-treatment (delayed randomization) design allows assessment of treatment engagement, clinical outcomes, durability of benefit, and the effects of re-treatment in the home setting. This hybrid design allows for evaluation of both immediate and sustained effects of the intervention, as well as the potential benefit of reintroduction following initial use. Spanning ~52 weeks, the study follows a decentralized design without traditional clinical trial sites. In-person assessments are conducted at more than 30 designated physical assessment center locations across the USA, chosen to ensure broad geographic representation of the population.

Step 1: All participants receive 12 weeks of MR-001 intervention (30 min per session, three times per week), followed by a 12-week washout. The 12-week intervention period was selected based on (1) extending the established evidence that users do not plateau after 5 weeks of MR-001 intervention [36] and (2) stroke rehabilitation evidence supporting this duration as effective for achieving clinically meaningful gains in walking capacity [40]. This timeframe also aligns with guidelines recommending sustained, task-specific therapy to support neuroplasticity and motor learning [14], and reflects typical US outpatient rehabilitation reimbursement models, which frequently authorizes approximately 36 therapy sessions over 12 weeks [41]. Participants self-administer MR-001 in their home environment, with remote support provided by the study team throughout the 12-week intervention period.

Step 2: At the end of the washout, participants are randomized 1:1 to either receive the MR-001 intervention for another 12 weeks followed by 12 weeks of washout, or continue with an additional 24-week washout. Participants and investigators are unblinded to the Step 2 allocation, but in-person assessors remain blinded.

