### Methods in analysis to handle protocol non-adherence and any statistical methods to handle missing data {20c}

Primary analysis will follow an intention-to-treat (ITT) approach, including all randomized participants in their assigned groups (for Step 2) regardless of adherence or protocol deviations. A per-protocol (PP) analysis will also be performed, excluding participants with major protocol violations.

Missing data will be handled under the missing at random (MAR) assumption. For the primary endpoint, participants who initiate the intervention but discontinue before completion will be classified as non-engaged. For secondary and exploratory outcomes, longitudinal analyses will use linear mixed models (LMM), which inherently accommodate incomplete follow-up data without the need for additional imputation by maximum likelihood estimation. This approach includes all available observations while appropriately addressing missingness conditional on observed data.

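### The only stated re-treatment analysis is an uncontrolled before-after change, and the randomised cohort A versus cohort B contrast is not specified

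*Protocol article*

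**What the plan says.** The Objectives section lists, as exploratory, "the effects of a second period of treatment on walking endurance and general mobility following a 3-month no-intervention period". Under Trial design, Step 2, "participants are randomized 1:1 to either receive the MR-001 intervention for another 12 weeks followed by 12 weeks of washout", and the alternative is a further 24 weeks of washout. The Participant timeline section adds "Outcome assessments are repeated at weeks 36 and 48". Table 1 schedules the 6MWT and TUG at both visits without limiting them to one cohort. The blinding section keeps in-person gait assessors blind to cohort.

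The Exploratory analyses section has an item headed as durability of re-treatment. Its population is "Among participants who undergo a second round of intervention following the withdrawal phase", and its contrast is that "changes in walking mobility and endurance will be compared before and after re-treatment to assess whether the intervention effect can be re-established". The TUG item in the same list asks "whether gains are maintained after withdrawal or re-established with re-treatment" and names no comparator. The section on non-adherence and missing data describes an intention-to-treat approach "including all randomized participants in their assigned groups (for Step 2) regardless of adherence or protocol deviations", but attaches no contrast to it.

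**The concern.** Step 1 is single-arm, so Step 2 holds the trial's only concurrent control. The stated objective concerns the effect of a second treatment period. The stated analysis uses cohort A alone and compares people with themselves, so cohort B contributes nothing to it.

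By week 24 each participant has been scheduled for four 6MWTs (screening and weeks 12, 16 and 24), and week 36 is the fifth. Physical therapy, occupational therapy and general exercise are permitted. A change from week 24 to week 36 in cohort A therefore mixes any device effect with retest effects, time trend and other background change. If that change is read as the effect of re-treatment, drift in either direction is credited to the device or set against it.

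The item's heading does not fit its content either. For Step 1 the article uses durability to mean retention after device use stops. Before versus after re-treatment measures renewed response. Retention after the second course concerns weeks 36 to 48.

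**Working it through.** **The plan's own figure.** The only power figure is for the primary endpoint: 98%, one-sided alpha 0.05, null 60%, true rate 72%. An exact binomial test with N = 225 rejects at 148 or more (exact alpha 0.0435) and has power 98.3%, so the figure reproduces. It concerns engagement. No sample size or power is given for Step 2, so no stated figure is contradicted here.

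**Inputs.**
- From the article: about 180 completers, so 180/2 = 90 per cohort at 1:1; half-MCID 17.2 m, so MCID 2 × 17.2 = 34.4 m.
- Assumed, not in the article: SD of 6MWT change from week 24 to week 36, set at 40 m with a range of 30 to 80 m and taken as equal in both cohorts; a drift d common to both cohorts of +5 or +10 m; two-sided alpha 0.05.

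**Before-after test in cohort A with no device effect.** SE = SD/√90. Probability of significance = Φ(d/SE − 1.96) + Φ(−d/SE − 1.96). At SD 40 m, SE = 40/√90 = 4.22 m. For d = 10, 10/4.22 = 2.37 and Φ(0.41) = 0.66.

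**Cohort A minus cohort B.** SE = SD × √(2/90). At SD 40 m, SE = 5.96 m and the 95% half-width is 1.96 × 5.96 = 11.7 m. Power for 17.2 m = Φ(17.2/5.96 − 1.96) = Φ(0.92) = 0.82. A common drift cancels, so the false-positive rate stays at 5%.

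| SD of change (m) | Before-after, d = +5 | Before-after, d = +10 | A−B 95% half-width (m) | A−B power, 17.2 m | A−B power, 34.4 m |
|---|---|---|---|---|---|
| 30 | 35% | 89% | 8.8 | 97% | >99% |
| 40 | 22% | 66% | 11.7 | 82% | >99% |
| 50 | 16% | 48% | 14.6 | 64% | >99% |
| 60 | 12% | 35% | 17.5 | 48.5% | 97% |
| 80 | 9% | 22% | 23.4 | 30% | 82% |

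The middle two columns are false-positive rates, which should be 5%.

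**Drift the other way.** Suppose the device effect is 17.2 m and untreated drift is −10 m. The expected before-after change is 17.2 − 10 = 7.2 m. At SD 40 m the chance of significance is Φ(7.2/4.22 − 1.96) = Φ(−0.25), about 40%, against about 98% with no drift.

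**Precision.** At SD 40 m the before-after half-width is 1.96 × 4.22 = 8.3 m, against 11.7 m for the cohort contrast. The contrast is wider by a factor of √2, before any gain from adjusting for the week-24 value.

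**The case against.** A reader might infer that the randomised comparison will never be made. The article does not support that. Its list of exploratory analyses is introduced as inclusive and not exhaustive. The intention-to-treat statement refers to assigned groups in Step 2, which implies some analysis by cohort, and blinding of assessors and analysts points the same way. The statistical analysis plan is not shown and may contain the contrast. What can be said is that the article does not specify it.

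A reader might also infer an as-treated analysis in open conflict with intention to treat. That is one reading only. The phrase about people who undergo a second round may simply mean cohort A, and the intention-to-treat sentence opens by referring to the primary analysis. The two sections do not fit together well, but a contradiction is not established.

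It can fairly be said that a within-person change answers a question the protocol asks, namely whether a person's gain returns on reintroduction. That stands, and it is a reason to keep the analysis as a description. It does not answer the objective about the effects of a second treatment period.

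The cohort contrast should not be oversold either. Participants and investigators know the Step 2 allocation, so comparing A with B does not remove expectation, or concomitant therapy that comes to differ after open allocation. It removes drift and retest effects common to both cohorts.

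The SD and drift are assumed, and the fifth test may bring little further practice gain. These points limit the numbers. They do not affect the structural point.

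**Conclusion.** The point holds as a defect of specification. The one re-treatment contrast that the article fixes is uncontrolled, and it leaves unused a randomised control already built into the design. This goes beyond detail left to an analysis plan, because the article positively states a weaker contrast than its design allows.

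The size depends on figures outside the article. For +10 m of common drift and no device effect, the before-after test is significant about 66% of the time at an SD of 40 m, and between 89% and 22% across SDs of 30 to 80 m. Negative drift would hide benefit. With 90 per cohort, the randomised contrast would have 82% power or more for one MCID (34.4 m) at SDs up to 80 m.

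Severity is moderate. Re-treatment is exploratory throughout, and a reader should not infer any threat to the engagement endpoint, its power or the secondary analyses.

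**What to change.** State the Step 2 contrast as cohort A minus cohort B in 6MWT and in TUG at week 36, in all randomised participants as assigned. Use an LMM with a cohort-by-visit term, or ANCOVA, adjusted for the week-24 value. Report the week-48 cohort difference as durability of re-treatment. Keep the before-after change in cohort A as descriptive, and correct its heading so that it no longer refers to durability. Say in the text that the open-label contrast does not remove expectation or differential concomitant therapy.

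This costs wording only, since the visits are already scheduled in both cohorts. The price in results is that the between-cohort estimate may be smaller, and will probably be less precise, than the before-after change. The Trial status section expected final data lock in October 2025, so the change should be dated against access to Step 2 results by cohort. If it comes after that access, it should be disclosed as such. If the analysis plan already contains the contrast, the article need only say so.
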